### Healthy Conversation Skills ‘lite’ training

This evaluation utilises existing scheduled HCS ‘lite’ training (a shortened version of the original HCS training) delivery across Portsmouth, delivered by author [name]. Table 2 provides a full description of the HCS ‘lite’ training according to the template for intervention description and replication (TIDieR) checklist [36]. HCS training is based on social cognitive theory [37,38], aiming to build trainees’ self-efficacy and confidence to have MECC conversations, and experiential learning, focusing on learning by practising and experiencing HCS [39]. Subsequently, HCS training (including HCS ‘lite’) includes practise, modelling of the skills by the trainer, opportunities for reflection, and supportive group learning [39]. The training content focusing on teaching the HCS philosophy (that is framed around motivating individuals to identify their own solutions) and the core healthy conversation skills to be applied to conversations. These four skills are; active listening (listening more than you speak), asking open discovery questions (ODQs) (open questions that spark motivation in that person and encourage them to come up with their own solutions), reflecting on practice, and facilitating SMARTER goal setting (helping people to set goals that are Specific, Measurable, Achievable, Relevant, and Time-bound, that are evaluated and reviewed at a later date) [25]. The underlying message of the philosophy is to encourage and empower individuals to support their own wellbeing through positive behaviour change, as opposed to passively supporting them (e.g., through merely listening and providing empathy) or providing advice [23]. HCS ‘lite’ training is focused on creating a supportive and non-judgemental setting. Although HCS ‘lite’ (a single training session) is pragmatically favoured to optimise the number of individuals who are able to attend, this means that there is no opportunity to implement HCS between sessions and therefore reflect on any alterations made to one’s practice within the training, which is concerning given that reflection is an important pillar of HCS training [39].

**Table 2 pone.0346348.t002:** Description (and programme architecture) of HCS ‘lite’ training organised using the template for intervention description and replication (TIDieR) checklist.

TIDieR checklist item	Description
Name of the intervention	Healthy Conversation Skills ‘lite’ training
Why	• Based on social cognitive theory and experiential learning pedagogy. The goal is to provide trainees with the confidence to deliver healthy conversations, by immersing themselves in the skills and approach. • The philosophy is focused on four main pillars; 1) I am not responsible for the choices people make, 2) Being given information alone does not make people change, 3) People come to us with solutions, and 4) It is not possible to persuade people to change their habits. • The four target skills are; asking open discovery questions (ODQs), active listening, supporting SMARTER goal setting, and reflection on practice.
What	**Procedure:** • The training begins by centring itself around the unifying motivation to help people. The concept of MECC and its benefits are introduced briefly. The philosophy and skills are introduced using interactive activities. • Throughout the training, trainees are encouraged to think holistically about their own wellbeing and what they could do to support it. E.g. trainees practise having a healthy conversation in pairs before and after the training content, and are encouraged to audio-record the conversations to listen back and reflect on them as a pair. • Scenarios are presented and trainees are asked to respond by text on their phone and self-assess their response in accordance with the HCS approach. To facilitate psychological safety, HCS ‘lite’ deliberately does not include group feedback or modelling of an incorrect approach to a conversation. • Trainees map influences of health onto the Dalgren and Whitehead social determinants of health model [40] during a group activity. • Trainees are encouraged to consider one thing they will implement after the training. **Materials:** A SMARTER goal setting sheet is provided. After training, trainees are provided with a cue card containing the philosophy and key skills.
Who Provided	Mostly a Public Health Practitioner from Portsmouth City Council. Some sessions delivered to undergraduate pharmacy students adopt a ‘train the trainer’ approach whereby previous cohorts of undergraduate pharmacy students were trained by [name] to deliver HCS ‘lite’ training to their peers.
How	In person, group-based (to allow for peer learning and support), usually in groups of around 6–30 people. Chairs are formed in an arc so that all trainees face each other, to facilitate discussion, avoiding use of notes and laptops, and aiding a supportive and non-judgmental group setting.
Where	Where all trainees are from the same organisation, training is delivered within a collaborative room within that organisation. For mixed groups (e.g., from some VCSE service providers), a room is booked that is accessible to all trainees (e.g., in a council building).
When and How Much	One three-hour session.
Tailoring	‘Train the trainer’ sessions are sometimes tailored so that undergraduate pharmacy students can take ownership of the training.
Modifications	Due to timetabling, undergraduate pharmacy students generally receive HCS ‘lite’ training in large groups, whilst VCSE service providers often attend HCS ‘lite’ training as part of a mixed group containing service providers from a range of professions, although the training is also often delivered to specific VCSE organisations.

Table 1 in Nichol et al. [21], which depicts regional MECC training according to the TIDieR checklist, illustrates the contrast with HCS training. Whilst both provide information about MECC and discuss health inequalities, regional MECC training focuses on providing information that can enable trainees to provide advice, whilst HCS (including HCS ‘lite’) training focuses on the skills needed to encourage individuals to identify their own needs for behaviour change.

### Development of initial programme theories (IPTs)

The development of IPTs for this realist evaluation was an iterative process, via four stages; 1) initial programme theory development based on retroduction and abductive reasoning [41], 2) refinement through informal literature scoping, 3) refinement through stakeholder involvement, and 4) prioritising IPTs.

Initial programme theory development began with drafting an overall theory of change for HCS ‘lite’ training, using Miro [42] to aid a mind mapping exercise. Initial ideas were organised into C, M, and O, and some initial tentative CM links were formed. This exercise began at the bottom level of abstraction (e.g., considering specific users) and informed more generalisable statements and proposed CM links, although at this stage no CMO configurations were complete as specific outcomes had not yet been configured. Mind maps were used to facilitate the grouping of contexts, mechanisms, and outcomes into more abstract and generalisable statements. This process also organised rival theories about when HCS ‘lite’ might not work, again organised by C, M, and O. This process also generated overarching inferences about how HCS ‘lite’ training works differently for different groups.

Next, scoping of the available literature on all iterations of HCS was conducted. Insights from the literature were systematically recorded into a table, organised by; study design, who (the sample), what (characteristics of HCS training), What worked (plus any thoughts about why), What did not work (plus any thoughts about why), and suggestions for programme theories (insights to inform the IPTs). Miro was again used to further develop higher order statements and start to link C, M, and Os. The statements were copied into a word document to facilitate linking of dyads (CM, CO, MO) and triads of CMO configurations. To further facilitate this process and help to illustrate how CMO configurations may interact with one another, a visual overall programme theory was created and then split and developed for each participant group specifically (VCSE service providers and undergraduate pharmacy students). Finally, a table was created to present CMO configurations alongside rival CMO configurations that illustrated how the outcomes could be different when the context was different, due to a differential triggering of mechanisms (see S3 File). Throughout this process, a list of potentially relevant substantive theories (substantive theories (mid-range theories from specific domains that explain how and why mechanisms operate) was created, which will be revisited throughout data analysis. Use of existing substantive theories within realist evaluation facilitates the process of developing CMO configurations and enables knowledge translation by contributing to the evidence base to inform other programmes, beyond HCS training [43].

Stakeholder involvement further refined the IPTs. The initial CMO configurations and overall visual programme theories were shared with the deliverer of HCS ‘lite’ training (author [name]) and were refined iteratively until both authors agreed (BN and [name]). These were also shared with the study team (all authors) which further provided suggestions for refinement. Formal stakeholder involvement consisted of meetings with two groups of stakeholders; one with key decision-makers involved in the implementation of HCS (both original HCS and HCS lite) in the South East of England (henceforth referred to as stakeholders), and one with those who had received HCS ‘lite’ training (henceforth referred to as service providers). Stakeholders’ (n = 4; 3 female, 1 male) involvement in HCS covered its design, delivery, and implementation, including specifically within the VCSE. Due to attrition, all service providers (n = 3; all female) were undergraduate pharmacy students. Initial involvement of both groups highlighted two crucial areas of focus; 1) engaging individuals to attend HCS ‘lite’ training, and 2) adopting the HCS approach long-term. The initial IPTs were further edited, removed, and added to following stakeholder involvement. For example, an initially proposed mechanism was that during the ‘lite’ training, it is essential to be able to plan implementation of the HCS, and anything that is not planned will not be implemented. The feedback from both groups was that behavioural cues (e.g., discussions with colleagues, HCS posters, emails about HCS) after the training to prompt memory and associate current practice with the training was more important than forming intentions and planning during the training. Stakeholder involvement also helped to identify key differences in CMO configurations based on the participant group. For example, whilst the programme theories initially focused on comparing trainees with healthcare backgrounds (undergraduate pharmacy students) versus non-healthcare background (service providers from the VCSE), stakeholder involvement highlighted that a comparison was between trainees who have lots of experience with talking to service users (i.e., VCSE service providers) versus those who had much less experience (undergraduate pharmacy students).

Finally, a pragmatic approach to prioritising IPTs was taken [44], selecting IPTs according to priority areas identified through stakeholder involvement (engagement of trainees to attend HCS ‘lite’, and implementing HCS in practice long-term), ‘weak spots’ or areas where the desired outcome is not always produced, areas judged to show potential for the greatest public health impact (e.g., through facilitating behaviour change at scale), and holistically capturing outcomes of HCS ‘lite’ (from attending training to long-term change). Most importantly, IPTs were prioritised according to their relevance outside of the specific programme (HCS ‘Lite’ training) [45]. Prioritisation resulted in 13 IPTs which were thematically grouped into five categories that describe different stages of HCS ‘lite’ training: 1) engagement (attending), 2) engagement (attention), 3) acquisition during training (pre-requisites to MECC delivery, e.g., competence, confidence, and motivation), 4) applying the skills (delivering MECC), and 5) habit formation. The overall visual programme theory is shown in Fig 1 (see S1 and S2 for the overall visual programme theories for each participant group), and the IPTs are shown in S3 File. The overall IPT states that:

**Fig 1 pone.0346348.g001:**
[figure not shown]
Visual depiction of the overall initial programme theory, for testing.

*An individual engages with HCS because they are supported to by their organisation and the training is framed around their personal motives. HCS ‘lite’ training helps people to deliver health behaviour change conversations because trainees exchange their existing communication style with a new proactive and motivational approach, through reflection and immersion in the skills. However, to translate intention to delivery after HCS ‘lite’ training, trainees must feel that the HCS approach is a social norm within their organisation and thus safe to deliver, or be prompted through environmental cues and reminders, which is particularly impactful if trainees have already planned to deliver HCS during the training. Facilitation of SMARTER goal setting is not maintained because it does not align with an opportunistic approach, and so most trainees are ill equipped to implement this skill within their roles.*

These propositions are exploratory, intended to be refined through iterative qualitative analysis and supported by quantitative data, consistent with the realist methodology.

### Quantitative pre- and post- survey

The quantitative before and after survey will be administered pre (immediately before receipt of training), post (immediately following training) and follow-up (8–10 weeks after training) to both participant groups. Opportunity sampling will be employed, such that all eligible trainees within the study period (August 2025 to April 2026) will be invited to complete the surveys. Where possible, the trainer ([name]) or coordinator of the training (e.g., a key contact at the University) will send the pre survey to trainees around 1 week before training. A QR code to complete the pre survey will also be displayed on the first slide of the training, with time provided at the start of the training for trainees to complete it. At the end of the training, a QR code to complete the post-survey will be provided and all trainees will be asked to complete it. Trainees will be encouraged to complete the post survey before leaving the training site, or at least within the next 24 hours following training (although will be able to access the link at any time). Eight weeks after the training, the trainer or coordinator of the training will send trainees a link to complete the follow-up survey. Since training to VCSE service providers is often as part of mixed professional groups and to avoid isolation of VCSE service providers, all attendees of mixed groups containing VCSE service providers will be invited to complete the surveys. Using Gpower to calculate the total sample size required to detect a significant difference in confidence, perceived usefulness, perceived importance, and competence between trainee groups, to detect a small effect size (0.3) at 80% power, a minimum total sample size of 352 (176 in each group) is required to detect a significant difference in confidence and competence post training between participant groups (two groups t test (correlations not available to calculate for multiple linear regression), two tailed, p < .05). With an added 10% margin to account for missing data (that is not missing at random), the target sample size is 387 (194 per group). If the target sample size is not reached, the available data will be analysed acknowledging that the analyses was underpowered as a limitation. As secondary analyses, differences pre and post within each group will also be tested.

Details of the survey items are available in the OSF pre-registration (https://osf.io/wpbn3/files). The consent form is embedded in the pre-survey following the participant information sheet and participants who do not consent will be automatically redirected to the end of the survey. Thus, written informed consent will be obtained. Participants will be reminded at the start of the post- and follow-up survey that their participation indicates their continued consent. To link each participant’s responses to the three survey timepoints, participants will be instructed to create a structured code to re-enter at each survey timepoint. Aside from demographic information (e.g., age, gender, experience) which will be collected within the pre survey, the questionnaire is identical across the three timepoints. Perceived usefulness of MECC, perceived importance of MECC, confidence to deliver MECC conversations, and competence of using ODQs will be assessed using existing measurement tools employed in other evaluations of HCS training [23,25–28]. Additionally, the existing competence tool [28] has been adapted for the current study to also assess competence in facilitating SMARTER goal setting. Both measures of competence present four scenarios (e.g., “*I’ve lost count of the number of times I’ve tried to stop smoking—it’s hopeless*!”) and ask participants to respond (in writing) as if they were having a real conversation with a client. After stakeholder involvement, a question was also included in the post-training survey timepoints to assess memory of the HCS philosophy. Each survey will take between 15–20 minutes to complete. At the end of the follow-up survey, survey participants will be invited to a) sign up to enter into a prize draw to win a £100 (first place), £50 (second place) or £25 (third place) Love2Shop voucher and b) complete an expression of interest form to take part in an interview.

Quantitative data will be analysed using SPSS [46]. To create a mean score for competency of ODQs and SMARTER goal facilitation, responses to the four scenarios for each skill will be aggregately coded by two independent coders (BN and another author), using established coding matrices adapted from previous studies [28]. Any discrepancies will be resolved through discussion with a third independent reviewer ([name]). Thus, aggregate scores (mean score across the four scenarios) will be calculated for both skills. Recall of the HCS philosophy will also be scored by two independent coders (BN and another author) and resolved through discussion with a third reviewer ([name]), using a self-created rubric available in the OSF pre-registration: https://osf.io/wpbn3/files. The data from attendees who are not undergraduate pharmacy students or service providers from the VCSE will not be included in the inferential analyses but will be summarised descriptively. Descriptive statistics will be produced for demographic characteristics, and pre and post scores relating to confidence, perceived usefulness, perceived importance, and competence (for both VCSE service providers and undergraduate pharmacy students). Exploratory baseline differences between professional groups for confidence, perceived usefulness, perceived importance, and competence will be tested through independent samples t-tests (or Mann-Whitney U tests if assumptions for an independent samples test are not met, tested using the Shapiro-Wilk test and Levene’s test for homogeneity of variances). Exploratory differences between trainee groups in post HCS ‘lite’ training (post survey) responses for perceived usefulness, perceived importance, and competence will be tested using a multiple logistic regression, controlling for baseline values (pre survey), age, and gender. Changes in confidence, perceived usefulness, perceived importance, and competence pre and post HCS ‘lite’ training will be tested within groups (conducted for both VCSE service providers and undergraduate pharmacy students) through within-subjects t-tests (or Wilcoxon Signed Rank tests If normality assumptions are not met, tested using the using Shapiro-Wilk test). Statistical testing will aid comparison with the existing literature of how HCS impact the confidence and competence of trainees across different settings. For the current realist evaluation, statistical testing will look to test (refine, support, refute) the IPTs, and therefore analysis will look to ‘preserve’ the configurations in analysis. For example, comparison across participant groups (undergraduate pharmacy students and VCSE service providers) will be tested for a relationship with proposed outcomes (motivation, competence, and confidence). If quantitative variables do not meet normality assumptions, non-parametric tests will be applied.

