### Study design

This study is a concurrent mixed methods realist evaluation, consisting of two methods of data collection: 1) a quantitative before and after survey, and 2) qualitative interviews with trainees. Both methods of data collection will sample VCSE service providers and pharmacy students evenly, for comparison. The quantitative survey will be used to generate data on the extent and distribution of outcomes and how these differ between VCSE service providers and pharmacy students (context) [35], whilst the realist interviews will help to explain how and why these outcomes are produced, by linking them to CMO configurations. The quantitative survey was designed to be complimentary to existing evaluations of HCS training, to also aid comparison between groups of trainees [25,28,31]. A between-subjects design for the quantitative survey will aid comparison between participant groups. Ethical approval has been obtained from Northumbria University prior to recruitment and data collection (Project ID: 10429).

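### Training is delivered in group sessions, but the sample size and the post-training and pre-post tests treat trainees as independent, so the nominal 5% error and 80% power do not hold if outcomes correlate within sessions

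*Protocol article*

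**What the plan says.** The sample size is in the section on the quantitative pre- and post- survey. The aim is "to detect a small effect size (0.3) at 80% power", the method is "two groups t test (correlations not available to calculate for multiple linear regression), two tailed, p < .05", and the result is that "a minimum total sample size of 352 (176 in each group) is required". A 10% margin for missing data follows: "the target sample size is 387 (194 per group"). No other allowance is made. The Study design section adds: "Both methods of data collection will sample VCSE service providers and pharmacy students evenly, for comparison".

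The same survey section names the tests:
- Baseline group differences "will be tested through independent samples t-tests", or Mann-Whitney U.
- Post-training group differences use a regression on baseline value, age and gender.
- Pre-post changes within each group use paired t-tests, or Wilcoxon.

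None of these has a term for session or trainer, and no ICC or design effect is mentioned.

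Table 2 (the TIDieR description) gives the delivery format: "In person, group-based (to allow for peer learning and support), usually in groups of around 6–30 people". Its Modifications row says that "undergraduate pharmacy students generally receive HCS ‘lite’ training in large groups", whereas VCSE providers often attend sessions mixed across professions or sessions run for one organisation. Most sessions have the same kind of trainer, but some pharmacy sessions are led by trained student peers.

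**The concern.** People trained in the same room share a trainer, a discussion and often an employer or year group. Here the group process is meant to work: Table 2 gives peer learning as the reason for the format, and the overall initial programme theory makes organisational support and social norms drivers of outcome. Some within-session correlation should therefore be expected.

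Sessions also appear to be largely nested within the compared groups. Pharmacy students mostly train together, and the VCSE mixed sessions are described as mixing professions. In that structure session variance does not cancel out of the group difference, and adjusting for individual baseline, age and gender does not remove it.

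Tests that ignore this declare group differences too readily. The Triangulation section turns survey results into context-outcome statements that are coded alongside the interview transcripts, so a spurious difference between VCSE providers and students could enter the programme theory as support for a context effect.

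**Working it through.** **Inputs from the article.** Effect size 0.3 (SD 1), two-sided 5%, 80% power, 176 per group, sessions of about 6 to 30.

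**Inputs assumed.** ICC of 0.01, 0.02 or 0.05; analysed pharmacy sessions of 30 (top of the stated range); analysed VCSE sessions of 12 (not stated anywhere); sessions fully nested within groups.

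**Step 1: the plan's own figure.** The exact two-group t-test solution is 175.4 per group, so 176 per group and 352 in total, with power 0.801. The margin is 352 × 1.1 = 387.2 and 176 × 1.1 = 193.6. The arithmetic reproduces; independence is the only problem.

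**Step 2: design effects.** DE = 1 + (m − 1) × ICC.
- Standard error assumed by the plan: √(2/176) = 0.1066.
- True standard error: √((DE₁ + DE₂)/176).

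| ICC | DE, m = 30 | DE, m = 12 | Mean DE | True SE |
|---|---|---|---|---|
| 0.01 | 1.29 | 1.11 | 1.20 | 0.1168 |
| 0.02 | 1.58 | 1.22 | 1.40 | 0.1261 |
| 0.05 | 2.45 | 1.55 | 2.00 | 0.1508 |

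**Step 3: the unadjusted test.**
- Type I error = 2 × (1 − Φ(1.96/√mean DE)).
- Power = Φ((0.3 − 1.96 × 0.1066)/true SE). The numerator is 0.0911.

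**Step 4: a valid session-level test.** There are 176/30 + 176/12 = 5.9 + 14.7 = about 20.5 sessions, so about 18.5 degrees of freedom. Power comes from the non-central t distribution with non-centrality 0.3/true SE (2.57, 2.38, 1.99).

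| ICC | Unadjusted: type I error | Unadjusted: power | Cluster-adjusted: power | Effect detectable at 80% (adjusted) |
|---|---|---|---|---|
| 0.01 | 7% | 78% | 68% | 0.35 |
| 0.02 | 10% | 76% | 62% | 0.37 |
| 0.05 | 17% | 73% | 47% | 0.45 |

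The two power columns belong to different tests. The unadjusted test keeps more power only because it rejects too often. Part of the loss in the adjusted column comes from the small number of sessions: with a normal reference, Φ(0.3/true SE − 1.96) gives 73%, 66% and 51%.

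**Step 5: other session sizes, equal in both groups.** Adjusted power here uses the effective sample size 176/DE; the figure with limited degrees of freedom is in brackets.
- m = 6, ICC 0.01: adjusted power 78% (77%), unadjusted type I error 5.6%.
- m = 18, ICC 0.05: 54% (50%), 15%.
- m = 30, ICC 0.05: 43% (37%), 21%.

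If all 387 were analysed (194 per group), adjusted power by effective sample size is 82% and 80% at m = 6 with ICC 0.01 and 0.02, but 74% and 47% at m = 30 with ICC 0.01 and 0.05.

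**Step 6: the other tests.** A paired test averages change scores over trainees within one group, so any session correlation in change inflates its variance by the same DE formula. Baseline scores are collected before the session, so only shared organisation or cohort can correlate them.

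**The case against.** **The size is assumed.** The article gives no ICC and no VCSE session size. Non-target attendees of mixed sessions are excluded from inference, so analysed VCSE clusters may be smaller than attendance. This stands. The direction is firm for any positive ICC; the size is not.

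**Baseline adjustment may recover power.** The post-training comparison adjusts for baseline, and the sizing takes no credit for that. With an assumed pre-post correlation of 0.5, residual variance falls to 1 − 0.25 = 0.75. The net variance factor is then 0.75 × 1.40 = 1.05 at ICC 0.02 and 0.75 × 2.00 = 1.50 at ICC 0.05. This stands in part: a net power loss is not established at low ICCs. It does not cure the inflated type I error.

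**The survey is exploratory.** The between-group tests are labelled so, and the article says that the survey will not statistically test the programme-theory configurations. This stands and lowers the severity. Yet the analysis text also gives statistical testing a part in supporting or refuting the theories, and an 80% power figure is stated.

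**Underpowering is already acknowledged.** The article does so only if the target number is missed. Clustering acts at the target number too, and that caveat does not address type I error.

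**Stronger readings not supported.** A reader might infer that the planned test itself has only 47% to 68% power; those figures belong to a cluster-adjusted test. A reader might also infer that every test is equally affected, but the baseline comparisons are less exposed.

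**Conclusion.** The point holds. Training is group-based and sessions appear largely nested within the compared groups, yet the sample size and the post-training and pre-post tests assume independent trainees. With any positive session ICC, the unadjusted standard errors are too small and the 80% calculated for 352 is not reached.

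Under the assumed inputs (ICC 0.01 to 0.05, sessions of 30 and 12, 176 per group), the unadjusted between-group test has a type I error of about 7% to 17% and power of about 78% to 73%. A valid test would have about 68% to 47% before any gain from baseline adjustment. These figures use the two-group t test on which the article sized the study; a regression without a session term has the same weakness. At six per session and an ICC of 0.01 the effect is minor.

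A reader might infer that the survey findings would be invalid. The documents do not support that, because no confirmatory decision rests on these p-values alone. It should be fixed before analysis.

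**What to change.** 1. Record session membership on the surveys for remaining sessions. Reconstruct it for sessions held since August 2025 where possible, for example from training date, site or survey timestamp. The survey items are in the pre-registration, which is not shown, so a session field may already exist.
2. Analyse the post-training between-group and the pre-post outcomes with a random intercept for session, or with cluster-robust standard errors and a small-sample correction.
3. Replace the 80% claim with the power of 352 over a stated ICC range, such as 0.01 to 0.05, giving the assumed session sizes and any credit taken for baseline adjustment.

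The cost is wider intervals, a less favourable power statement and some work to reconstruct past sessions. With perhaps six pharmacy sessions the session variance will be imprecise, which is why the small-sample correction matters. No extra recruitment is needed, but the change makes the inference honest without restoring 80% power. Results are not due until March 2027, so there is time to change the analysis.
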